**Figure 1 Fig1:**
[figure not shown]
**Peer support for patients with type 2 diabetes in Nanjing--Consort diagram for diabetes project study design.**

### Ethics

Approval to conduct this study has been granted by the Committee on Human Research (Institutional Review Board) at Zhong Da Hospital, Southeast University (2012ZDLLKY05.0). Written informed consent was obtained from all trial participants after providing sufficient time to consider partaking in the study, read the details provided on the Patient Information Sheet, in addition to ask and have answered any questions pertaining to the trial.

### Eligibility criteria

#### Peer leaders

Inclusion criteria:Patients with type 2 diabetes and HbA1c ≤ 7.5%;Insulin injection experience is preferred,Can commit to attending a 20-hour training, organize activities with other patients every month and attend a leadership meeting at least twice a year,Have basic diabetes self-management knowledge and supportive, non-judgmental communication skills,Willing to lead.

Exclusion criteria:Patients with unstable mood or major psychiatric conditions,Physical disability or severe speech impediment which may influence communication with others,Patients with other serious health conditions (e.g., terminal cancer) or life expectancy less than 12 months,Illiteracy.

#### Patients

Inclusion criteria:Patients with type 2 diabetes,Declaration of voluntary participation in the study with signed informed consent form,Reside in local community during the intervention period.

Exclusion criteria:Patients with unstable mood or major psychiatric conditions,Patients with serious diabetes complications (e.g., blindness) that would impede meaningful participation in the program,Patients with other serious health conditions (e.g., terminal cancer) or life expectancy less than 12 months,Patients currently enrolled in other research program.

### Enrolment and randomization

#### Participants

Whether on self-recommendation or recommendation by clinicians and staff members, all peer leader candidates will follow a strict selection procedure from which eligible peer leaders are identified. Additional patients were also selected from primary health care settings and recruited from posted flyers. Primary care clinicians reviewed search results and excluded patients. The study team contacted eligible patients via phone calls to explain the study and arranged enrolment appointments.

#### Group allocation

Community health centres will be stratified by size and existing structure of primary diabetes care service. Allocation to intervention or control group is governed by a random number generation process using SAS 9.1 statistical software independently.

### Intervention

#### Peer leader training

Peer leaders are required to attend twenty-hour structured training programs in their community which were led by the study team. The training was conducted using a standardised training curriculum developed by the research team. The training team comprised of endocrinology physicians, certified diabetes educators (nurses), registered dieticians, exercise physiologists, psychiatrists, traditional Chinese medicine specialists, and communication trainers. The program aimed at enhancing diabetes knowledge and promoting diabetes self-care behavior. The Peer Leader Training (PLT) curriculum utilizes multiple educational approaches (such as lecture, practise, seminar and etc.) and consists of 5 major components. The content covers basic knowledge of diabetes, behavior change skills, and communication techniques, organisational management methods highlighting individual responsibilities and group management techniques, as well as psychological support.

#### Control group

The sessions for the control groups were interactive and informal. Participants were given a handbook that introduces issues in the training session. Patients attend the self-management training and communicate with the professionals every two months to obtain information on diabetes diet, exercise, glucose monitoring, etc. Additionally, group members will attend three follow ups at baseline, 6 months, and 12 months.

#### Intervention group

Patients are divided into groups of 8–15 people and assigned to peer leaders for 12 months according to their area of residence. In addition to receiving the same training and follow-ups as the control group, patients from intervention groups were suggested and encouraged to take part in monthly group activities with peer leaders. If possible, casual activities (such as phone calls, WeChat voice messages, physical exercises, group member’s family visits, shopping together, etc.) are also recommended. The first meeting is an introductory discussion of group members’s backgrounds and their disease history, through which the leaders established understanding and relationship with the peers. In subsequent interactions, the leader and peers will discuss the following issues: their current and target values for HbA1c, blood lipids and blood pressure; self management skills such as using a glucose meter and appropriate strategies for hypoglycaemia; lifestyle changes around healthy diets, physical activities, foot care, and stress control. The subsequent monthly activities include interactions designed by the research team, peer leaders, as well as college student volunteers. Several cultural group activities will be organized such as Chinese hand calisthenics and body calisthenics, how to choose daily nutritional meals, knowledge competition, and singing songs that were integrated with health education topics. Group members also shared similar experiences on lifestyle, family life, personal hobbies and experiences to support each other in achieving goals. Peer leaders documented each encounter and recorded each time the date, number of participants, the nature of encounter, approximate duration of contact, and topics discussed. In addition, peer leader meeting will be held every six months. In the leader meetings, peer leaders will share their experiences and discussed the problems they confronted in their groups. The research team will aid them discover the solutions and provide them with further training when necessary.

### Sample size calculation

Sample size and power calculations are performed for the main outcome of interest-difference in mean HbA1c levels-using effect sizes and standard deviations derived from multiple published trials of patient-education interventions. Using a non-inferiority design based on clinically relevant difference of HbA1c of 0.5%, standard deviation of 1.5, and groups of 8–15 participants per randomisation group for 80% power at two-sided 5% significance, 150 participants are required to complete the study procedures. Allowing for a 20% drop-out from randomisation to completion of the trial, it is anticipated that we would require 180 subjects in each arm to be randomised in the study.

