### Study design and setting

This study is a cluster randomised controlled trial implemented and reported in accordance with the requirements of the CONSORT statement [13] and its extension to cluster randomised trials [14]. The participants were randomly designated to either an intervention arm, which implements the usual care system and the peer support intervention, or a control arm which implements a usual care system, with geographical location being the unit of cluster randomisation.

All participants are patients with type 2 diabetes who receive primary health care at 12 rural community health centres located in Liu-he District, Nanjing, and Gao-gou Town, Huaian, in Jiang Su province. The study team coordinates and works hand-in-hand with the staff members at each community health centres to implement and monitor the study.

Figure 1 is a CONSORT diagram of the study design.

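### The stated 80% power is not supported for a cluster design: the sample size leaves room for a design effect of at most about 1.06, and its cluster size does not fit the 12 health centres

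*Protocol article*

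**What the plan says.** The Sample size calculation section takes a "clinically relevant difference of HbA1c of 0.5" percentage points, with an SD of 1.5. Its cluster size, power and required number are then given together: "groups of 8–15 participants per randomisation group for 80% power at two-sided 5% significance, 150 participants are required to complete the study procedures". The next sentence allows for 20% drop-out and arrives at 180 subjects in each arm, so I read the 150 as completers per arm. No ICC, design effect or number of clusters is given.

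The Study design and setting section makes geographical location the unit of cluster randomisation and describes the participants as "patients with type 2 diabetes who receive primary health care at 12 rural community health centres". The Group allocation section stratifies the health centres before allocation. The Intervention group section then says: "Patients are divided into groups of 8–15 people and assigned to peer leaders for 12 months according to their area of residence".

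The Data analysis section plans multilevel and repeated-measures analyses, with adjustment for clustering by site and provider where needed. It also plans an analysis of covariance of the 12-month values on baseline and arm.

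**The concern.** In a cluster randomised trial, the number of patients has to be inflated for correlation within the randomised units. The inflation depends on the size of those units and on the ICC. Here the only size given is 8–15. Elsewhere in the article that is the size of the groups assigned to a peer leader, while allocation appears to be by health centre or locality. The total of 150 is close to what individual randomisation would need, which suggests little or no inflation.

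What is at stake is the claim of 80% power for the primary outcome. Readers will judge a non-significant HbA1c result against that claim. If the figure rests on near-independence of patients within a centre, they should be told so.

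**Working it through.** **Inputs from the article.** Difference 0.5, SD 1.5, two-sided 5%, 80% power, 150 completers and 180 randomised per arm, 12 health centres.

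**Assumptions of mine.** Centres are the randomised units, 6 per arm and equal in size. The ICC is 0.01 to 0.05; the article gives none. I use 150 completers per arm throughout.

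**1. The plan's figure under individual randomisation.**
n per arm = 2 × (1.960 + 0.842)² × 1.5² / 0.5² = 141.3, so 142. The article names a non-inferiority design; with a margin of 0.5, a true difference of 0 and one-sided 2.5%, the answer is the same 142. A t-based version gives 143. None of these reproduces 150.

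**2. The design effect that 150 can absorb.**
150 / 141.3 = 1.062. With design effect = 1 + (m − 1) × ICC, the largest ICC covered is 0.062 / (m − 1):

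- m = 8: 0.0088
- m = 15: 0.0044
- m = 25: 0.0026

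**3. Size of the likely randomised unit.**
360 enrolled / 12 = 30 per centre; 300 completers / 12 = 25 per centre. This is two to three times the 8–15 that the calculation quotes.

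**4. Power with centres as clusters (m = 25, 150 per arm, unadjusted).**
SE = 1.5 × √(2 × DE / 150), where DE is the design effect. Normal-reference power = Φ(0.5/SE − 1.96). The t column uses a noncentral t with 12 − 2 = 10 df and noncentrality 0.5/SE.

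| ICC (assumed) | DE | SE | Power, normal | Power, t on 10 df |
|---|---|---|---|---|
| 0 | 1.00 | 0.173 | 82% | 74% |
| 0.01 | 1.24 | 0.193 | 74% | 65% |
| 0.02 | 1.48 | 0.211 | 66% | 57% |
| 0.05 | 2.20 | 0.257 | 49% | 42% |

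The normal column isolates the design effect. The t column adds the cost of having few clusters, which is present even at ICC 0: with 10 df and no adjustment, 80% is not reached at any ICC.

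**5. Difference detectable with 80% power.**
Normal reference, 2.802 × SE: 0.54, 0.59 and 0.72 at ICC 0.01, 0.02 and 0.05. With t on 10 df the multiplier is about 3.11, giving 0.60, 0.66 and 0.80.

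**6. The article's own group size as the cluster.**
At m = 8 to 15 and 150 per arm, normal-reference power is 80–77% at ICC 0.01, 77–72% at 0.02 and 70–60% at 0.05.

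**7. Crediting the planned baseline adjustment.**
With an assumed baseline-to-follow-up correlation of 0.6, applied within and between centres alike, the variance is multiplied by 1 − 0.6² = 0.64. At ICC 0.01, 0.02 and 0.05, power is about 90%, 84% and 68% (normal), or 83%, 76% and 59% (t on 10 df).

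**The case against.** The strongest reply is that the power may still be adequate. The analysis of covariance is planned, and step 7 shows that a correlation of 0.6 would restore 80% at ICC 0.01 on either reference, and at 0.02 on the normal one. A reader might infer from step 4 that the trial is underpowered and cannot reliably detect 0.5. The documents do not support that, because they give neither the ICC nor the correlation. What remains is that the sample size section takes no credit for the adjustment, so its 80% cannot rest on it.

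A reader might also infer that no design effect was used. That is not shown either: 150 exceeds 142, and a group size is listed among the inputs. A small undisclosed allowance is possible, but on these inputs it cannot exceed about 1.06. In a condensed article an unprinted ICC is no fault in itself. The point rests on that ceiling and on the mismatched cluster size.

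The centre as unit is an inference. The design section says geographical location, the Group allocation section stratifies centres without naming what is allocated, the abstract speaks of patients being randomised by community staff, and the calculation attaches 8–15 to a randomisation group. Nor does the article say outright that groups of 8–15 exist only in the intervention arm; the Control group section mentions groups but gives no size. Centres remain the likeliest reading, and step 6 shows the 80% is not secure under the other one.

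Finally, the 10-df loss is separate from the design effect, and the article fixes no df rule. That is fair, and the two are shown apart. The drop-out arithmetic (180 × 0.8 = 144, not 150) is also a separate matter and is kept out of the figures above.

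**Conclusion.** The point holds in this form: the 80% power does not follow from the design as described. Two parts need no assumed ICC. The sample size leaves room for a design effect of at most about 1.06, and the cluster size it quotes does not fit 12 health centres averaging about 25 completers.

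On the stated unadjusted inputs with a normal reference, 80% is kept only if the centre-level ICC is about 0.003 or less. The size of any shortfall is conditional. It rests on the assumed ICC range, a 6:6 split and equal centres; unequal centres would lower power further. It also depends on how much the baseline adjustment recovers. The supportable conclusion is that the 80% is unsupported, not that it is proven absent.

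**What to change.** Rewrite the Sample size calculation paragraph:

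- Name the randomised unit, and use the same term in the abstract, design, allocation and sample size sections.
- State the number of units per arm and the expected completers per unit, using one number of completers throughout.
- Give an explicit ICC range with its justification, the design effect 1 + (m − 1) × ICC, and a t reference suited to the small number of units.
- If the planned baseline adjustment is credited, state the correlation assumed.
- Replace the 80% claim with the resulting power across the ICC range, or with the difference detectable at 80% power.

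Enrolment and procedures do not change. The cost is one paragraph, and a stated power that will probably look less favourable.

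### Sample size: 180 randomised per arm with 20% drop-out leaves 144 completers, not the 150 the protocol requires (a minor correction)

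*Protocol article*

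**What the plan says.** All the figures are in the protocol article, Methods, Sample size calculation. The main outcome is the difference in mean HbA1c. The stated inputs are a "clinically relevant difference of HbA1c of 0.5" percentage points, a "standard deviation of 1.5" and "80% power at two-sided 5% significance". From these the section concludes that "150 participants are required to complete the study procedures". It does not say whether the 150 is per arm or in total.

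The next sentence sets the loss and the enrolment target: "Allowing for a 20% drop-out from randomisation to completion of the trial, it is anticipated that we would require 180 subjects in each arm". This target is explicitly per arm.

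**The concern.** The drop-out is defined as running from randomisation to completion, so its base is the number randomised. Someone who checks whether 180 per arm delivers the required completers at the stated loss finds that it does not. The required completers, the drop-out rate and the enrolment target appear in two consecutive sentences, and they cannot all be true.

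What is at stake is the planned number of evaluable patients for the primary outcome, and whether a reader can tell which of the three figures the trial is held to. The missing per-arm label on the 150 adds a small ambiguity in the same place.

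**Working it through.** **Inputs**, all from the Sample size calculation section: 150 required completers (read as per arm, see step 4), drop-out d = 0.20, 180 randomised per arm, difference 0.5, SD 1.5, two-sided 5% significance, 80% power. Equal allocation is implied by the same number in each arm.

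**1. Reproducing the 180.**
- Adding 20% of the completers: 150 × (1 + 0.20) = 180. This matches exactly.
- Allowing for 20% loss from those randomised: 150 / (1 − 0.20) = 187.5, rounded up to 188. This does not match.

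**2. What 180 delivers.**
- Losses: 180 × 0.20 = 36.
- Completers: 180 × 0.80 = 144 per arm, which is 150 − 144 = 6 short.
- Enrolment gap against the 20% target: 188 − 180 = 8 per arm, or 376 − 360 = 16 in total.
- Drop-out at which 180 still yields 150: 1 − 150/180 = 0.167, or 16.7%.

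**3. What the shortfall costs on the stated inputs, ignoring clustering.**
- Required completers per arm, normal approximation: n = 2(z₀.₉₇₅ + z₀.₈₀)² × SD² / difference² = 2 × (1.960 + 0.842)² × 2.25 / 0.25 = 141.3, so 142. The t-test version gives 142.2, so 143.
- The section labels the design as non-inferiority. With a margin of 0.5 and one-sided 2.5%, the result is also 142, so the label does not affect this check.
- Power by number of completers per arm:

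| Completers per arm | t-test | Normal approximation |
|---|---|---|
| 144 | 80.5% | 80.7% |
| 150 | 82.1% | 82.3% |

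The loss is 82.1 − 80.5 = 1.6 percentage points, and 144 still exceeds the 142 to 143 that the stated inputs need.

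**4. Is 150 per arm or in total?** Read as a total, it would be 75 per arm. Inflating 75 gives 75 × 1.2 = 90 or 75 / 0.8 = 93.75, so 94 per arm, and neither is near 180. Read per arm, 150 lies a little above the 142 to 143 needed for 80% power, and 180 follows from it by the factor 1.2. Only the per-arm reading fits.

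**The case against.** The strongest objection is that nothing material follows. The 80% target is still met at 144 per arm on the plan's own inputs, and no estimand, analysis or conclusion changes. That stands, and it sets the size of the point.

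It can also be said that 180 may have come from another route: 142 / 0.8 = 177.5, rounded up to 180. This is numerically possible, and because no formula is shown, the multiplication by 1.2 remains an inference from an exact match. It does not remove the inconsistency. The section states 150 required completers, not 142, and 180 does not yield 150 at 20% loss however it was derived.

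Two stronger readings are tempting, and the document supports neither.

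- A reader might infer that the surplus of 150 over about 142 is the plan's allowance for clustering, and that falling to 144 nearly exhausts it. The section lists groups of 8–15 among its inputs, but it gives no intracluster correlation or design effect and never describes the surplus that way. It could equally be rounding. Whether clustering is adequately allowed for is a fair question, but a separate one.
- A reader might take the unlabelled 150 as a total and conclude that the trial is badly underpowered, at about 53% with 75 per arm. No such trial is planned: 180 are to be randomised in each arm, and 144 remain after 20% loss. The missing label is an editorial fault.

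**Conclusion.** The three figures are inconsistent as written. With 20% drop-out after randomisation, 180 per arm gives 144 completers; 150 would need 188 per arm, and 180 suffices only up to 16.7% drop-out. This arithmetic rests on one assumption, that the 150 is per arm, and no other reading fits the rest of the section.

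The consequence is minor: 6 completers per arm and about 1.6 points of power, with power still just above 80%. The power figures assume the stated difference and SD, equal arms and independent patients. They are not the power of the cluster randomised trial, because the document gives no intracluster correlation from which to work that out.

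**What to change.** Correct the sentence in the Sample size calculation section:

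1. Label the 150 as per arm.
2. Keep 180 per arm and add one of two statements: that 144 completers per arm are expected at 20% drop-out, or that 180 per arm covers drop-out of up to 16.7% for a target of 150.
3. If a power is quoted for 144 (about 80.5%), mark it as not accounting for clustering. Without that note it would mislead, because the unit of randomisation is geographical location (Study design and setting).

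The cost is one reworded sentence. Under the first statement, the plan also gives a slightly less favourable completer figure. No change to enrolment, design or analysis is needed.

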### Data collection and outcome measures

Data will be collected at baseline, 6 months and 12 months for both intervention groups and comparison group. Table 1 shows the measurement tools of data collection, the method of data collection and the time points of data collection.

**Table 1 Tab1:** **Measurement domains, survey tools used at each data collection time point**

Variable	Measurement tools/questions	Base-line	6mth	12mth
Demographic measures	Sex, age, ethnicity, religion, education, occupation, health insurance, marital status, anual income, annual household expenditure	√		
Health status	Time of diagnosis, family history, complications and co-morbidities, smoking, alcohol intake, frequency of physical exercise, length of diagnosis with diabetes, health education access;	√		
	therapy, list of a prescribed medications, events of hypoglycemia	√	√	√
Psychosocial status	Diabetes knowledge	√	√	√
	Activities of self-management, (SDSCA)	√	√	√
	Self-efficacy (Diabetes Self-Efficacy Scale)	√	√	√
	Adherence to medication (Morisky Scale)	√	√	√
	Quality of life( EQ5-D, DDS)	√	√	√
	Life satisfaction(SWLS)	√	√	√
	Trait affect(PANAS)	√	√	√
	Depression, anxiety and stress( PHQ-9, DASS)	√	√	√
Biomedical measures	Weight, , height	√	√	√
	Waist circumference, hip circumference	√	√	√
	Blood pressure,	√	√	√
	HbA1c(glycosylated haemoglobin)	√	√	√
	AGEs( advanced glycation end products )	√	√	√
	Blood glucose (fasting plasma glucose and 2 hour post load glucose)	√	√	√
	Blood Lipids(total cholesterol, low density lipoprotein, high density lipoprotein, triglycerides)	√	√	√
Cost	Cost of medicine, travel time and fee, escort fee, hospital stays and fee, cost of services, etc.	√	√	√

Data collection consists of two main parts, questionnaire and biophysical data. The questionnaire data includes four main parts and will be collected by trained investigators. The first part covers social demographics (e.g., sex, age, ethnicity, religion, education level, occupation, health insurance, marital status, annual income, etc.); the second portion concerns measures of health status (eg, time of diagnosis, smoking, alcohol intake, frequency of physical exercise, therapy, length of diagnosis with diabetes, family history, complications and co-morbidities, educational history and type, glucose monitor). The third section is psychosocial status including knowledge of diabetes; activities of self-management [15], self-efficacy [16], adherence to medication [17, 18], quality of life [19–21], diabetes distress screening [22, 23], traits [24], life satisfaction [25], depression, anxiety and stress [26–28]. The final section asks about economic status, which covers training, equipment availability, human resources, drugs, travel fees, escort fees, communication expenses, consumables, etc.

The biophysical data are collected by specifically trained staff according to standard operation procedure. Height is measured using a portable height rod to the nearest 0.1 cm with the participants standing without headgear or shoes. Weight is measured to the nearest 0.1 kg using a calibrated, portable, digital weighing scale. Body mass in dex (BMI) is calculated as weight in kilograms divided by height in meters squared. Waist circumference is measured midway between the lowest rib and the top of the hip bone using the tape measure. Hip circumference is taken at the maximum circumference over the buttocks [29]. Duplicate waist and hip circumference measurement is taken for approximately 10% of the participants for quality assurance. Blood pressure meter and weight scales are calibrated at least weekly. Laboratories providing blood analysis are accredited, and all methods for determining HbA1c% are NGSP approved.

